Social media represents a promising strategy to deliver evidence-based smoking cessation interventions to young adults. Social media tools are widely popular among young adults (89 % of 18 to 29 year old Americans use the internet) [19] and can be harnessed to widely disseminate information about a broad range of behavioral and emotional changes including smoking cessation [20–23]. Facebook remains the most widely used social media tool by young adults in the United States. With 87 % of US online young adults having a Facebook account and 70 % of those accessing it daily [19], there is promise to use this platform to deliver public health intervention programs to young people. Previous evaluations using Facebook to change health risk behavior have shown feasibility as measured by participant’s engagement and satisfaction [24–32]. However, trials examining social media interventions have shown limited or no effects on health behavior change (e.g., physical activity) [33]. The BIO smoking cessation campaign for young adults in Canada, incorporating a website, Smartphone app and Facebook features, resulted in greater 7- and 30-day reported quit rates than referral to a Smokers’ Helpline at 3 month follow-up [34]. Research is needed to determine whether Facebook alone can be used as an intervention tool, whether abstinence can be biochemically verified, and whether abstinence rates can be maintained over 1 year.

Our group conducted a mixed-methods study to determine how young adult smokers would like to use Facebook to help change smoking behavior. About a third (31 %) of survey respondents reported they would want to quit smoking using Facebook, and interest was greater among those more motivated to quit, who had made a quit attempt in the past year, and had previously used the Internet for assistance with a quit attempt (all *p* < 0.01). In qualitative interviews, social support and convenience were identified as strengths of a Facebook intervention, while privacy was the main concern [35].

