### Study procedure

Informed consent is obtained from all study participants in accordance with the Helsinki Declaration and approved by the UCSF Committee in Human Research (#11-06294). During the informed consent process, participants’ understanding of the information provided is assessed through a series of multiple choice questions with required responses before being able to proceed with the study. Questions are based on those used in studies with potentially vulnerable populations [41, 42]. Any wrong answers during the consent process are sent to study staff who then contact a potential participant via email or Facebook for further clarification of the consent process. Therefore, no participant will be enrolled that has not answered all consent questions correctly. Participants consenting to participate in the study are asked to verify age by sending proof through email or social media. Verified participants are emailed a baseline assessment. Those completing the baseline assessment are randomized to receive either the Tobacco Status Project (TSP) intervention of referral to the Smokefree.gov website (control).

A stratified random assignment program was developed and participants are assigned from within stratified blocks immediately after completing the baseline assessment. Participants are stratified on stage of change (precontemplation, contemplation, preparation) and smoking pattern (daily vs. non-daily), variables known to be related to outcomes and addressed by the intervention [43]. Participants in the TSP group are assigned to “secret” (private) Facebook groups based on their readiness to quit tobacco. Groups begin when there are approximately 10 participants enrolled, as that has been deemed the optimal number based on analyses of engagement in our previous work [37] ([name], [name], [name]: Smoking cessation intervention on Facebook: Which content generates the best engagement?, submitted). Participants in the control condition are given a referral to the Smokefree.gov program and are encouraged to use it as much as they would like.

Assessments occur online using the survey program Qualtrics at baseline, 3, 6, and 12 months follow-up. Participants receive their choice of gift cards in the amount of $20 per assessment, and a $20 bonus for completing all three assessments, for a total possible stipend of $100 for completing all assessments.

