### Treatment conditions

#### Tobacco Status Project (TSP)

The TSP is a smoking cessation intervention implemented entirely through “secret” (Facebook’s word for entirely private) Facebook groups. All TSP participants are assigned to a Facebook group based on their TTM stage of change (precontemplation: not ready to quit in the next 6 months; contemplation: intending to quit in the next 6 months; or preparation: ready to quit in the next month and demonstrating at least one past year quit attempt).

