**Fig. 2 Fig2:**
[figure not shown]
Tobacco Status Project Sample Posts

Second, the intervention incorporates weekly “The [name] In” live sessions with a PhD level smoking cessation counselor (using FB commenting features), during which a counselor provides some limited content for discussion and participants can ask questions and get supplemental support. Content for sessions is tailored to readiness to quit tobacco and is based on Motivational Interviewing (MI) and cognitive behavioral coping skills for smoking cessation.

Third, six manualized 45-min state-of-the-art smoking cessation counseling sessions based on cognitive behavioral therapy (CBT) were adapted for social media delivery for this study. These sessions are designed to be delivered in Facebook events and events are scheduled in each group separately. In contrast to The [name] In sessions that are conversational and question and answer-based, these sessions present more material, and are designed to help participants who are motivated to quit. Thus, only participants in preparation groups are offered these CBT sessions and participants may opt to participate in the sessions at any time during the 90 days of Facebook intervention. In all groups, links to more intensive treatment in a participant’s’ area are available as needed.

Additionally, we are testing an incentive structure in which the TSP groups are randomized to one of four incentive conditions tied to engagement in the intervention: 1) daily; 2) weekly; 3) monthly; or 4) no incentive. Participants in daily, weekly, or monthly groups can earn money based on comments made to daily Facebook posts at the end of each period. At the end of the 90-day intervention, all participants in paid incentive conditions receive a gift card in the amount they have earned up to $90. This is separate from the $100 participants could earn for completing all study assessments.

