### Secondary outcomes

The following secondary outcomes will be assessed at each timepoint:**Reduction of cigarette consumption by 50 % or more (y/n)** between baseline each follow-up will be calculated from the number of cigarettes smoked in the past 7 days at each time point.**Tobacco quit attempt** (y/n). A *Follow-up Smoking Questionnaire* will assess the presence and number of 24 h quit attempts since the last assessment, used to calculate presence of at least one quit attempt in the assessment time period.**Readiness to quit tobacco** will be assessed using the *Stages of Change Questionnaire*, [44] categorizing participants into five stage categories at each timepoint (precontemplation, contemplation, preparation, action, and maintenance), and predictive of quit attempts and cessation [51]. Outcome will be measured as proportion in action or maintenance stage sof change at 3, 6, and 12 month assessments.**Abstinence goal** will be assessed with the *Thoughts About Abstinence Form, *[52]*,* categorizing goal as no goal, intermediary goal (e.g., reduced smoking), or total abstinence. Outcome will be measured as proportion endorsing a goal of abstinence at each timepoint.**Engagement in TSP** will be measured by total number of comments to Facebook study groups during the three-month intervention period.

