### Secondary analyses

Mixed effects logistic and multinomial regression models for longitudinal ordinal response data to model secondary outcomes for tobacco use and across time (3, 6, 12 months): 1) reduction of cigarettes by 50 % or more (y/n), 2) tobacco quit attempt (y/n; 2 models), 3) action or maintenance stage of change (y/n); and 4) commitment to abstinence (y/n). Independent variables in all models will be treatment condition, abstinence status, and covariates identified as relevant to smoking characteristics in the literature.

To evaluate the secondary aim (effect of a monetary incentive on engagement in the TSP condition), we will test for differences in engagement and primary smoking outcome by incentive groups and the relationship between engagement and primary smoking outcome at 3 months. First, due to expected skewed distribution of the engagement variable (comments), the non-parametric Kruskal-Wallace test will examine overall differences in total number of comments made to the Facebook study group by incentive condition, with test for a linear trend in commenting by incentive frequency. Second, Pearson’s chi-square test will examine 7-day point prevalence abstinence by incentive condition. Abstinence rates will be examined by incentive group. Two sets of analyses will be conducted: one for biochemically verified abstinence, and one for reported abstinence. Finally, Mann–Whitney U tests will compare comments for those abstinent at 3months to those non-abstinent. Again, two sets of analyses will be conducted (one for biochemically-verified abstinence and one for reported abstinence).

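### The engagement question is worded as an effect on abstinence but tested by an unstratified Mann-Whitney comparison, so differences between stages of change can produce a link where engagement has no effect

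*Protocol article*

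**What the plan says.** The Secondary Aim (Aims and hypotheses) lists three analyses. The third is worded as an effect of engagement on abstinence. Under Secondary analyses the same question becomes "the relationship between engagement and primary smoking outcome at 3 months", and the method is that Mann-Whitney "U tests will compare comments for those abstinent at 3months to those non-abstinent", run once for verified and once for reported abstinence. No stratum or covariate is named. The covariate provisions elsewhere under Data analysis concern the regression models, and a plain Mann-Whitney test cannot carry them.

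Secondary outcomes defines engagement as "total number of comments to Facebook study groups during the three-month intervention period". This is observed behaviour, not an assigned exposure.

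On stage of change:
- Study procedure makes stage and smoking pattern the randomisation strata and calls them "variables known to be related to outcomes and addressed by the intervention".
- Treatment conditions, Tobacco Status Project (TSP): "All TSP participants are assigned to a Facebook group based on their TTM stage of change". Posts are written separately for each stage, and "only participants in preparation groups are offered these CBT sessions".
- Background reports from a formative survey about quitting by way of Facebook that "interest was greater among those more motivated to quit".

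**The concern.** The test pools participants from precontemplation, contemplation and preparation groups. If preparation members both quit more and comment more, quitters will on average have more comments than non-quitters even if, within every stage, commenting makes no difference. The first link (stage to quitting) is stated in the protocol. The second (stage to commenting) is an inference from the design.

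At stake is how a positive result is read. With the aim worded as an effect, a significant difference in comments would invite the conclusion that engagement brings about quitting. The difference could instead come from a baseline factor that is recorded for every participant and already used for stratification.

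**Working it through.** The protocol gives no sample size, power or error rate for this test, so there is no figure of its own to reproduce. The check asks how often the planned test rejects when engagement has no effect within any stage.

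**Inputs from the protocol (Overview of design, Power calculation).** Total sample 480; 10% abstinence in the treatment arm; 50% attrition.

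**Assumptions.**
- 1:1 allocation (the ratio is not stated). TSP arm 480/2 = 240; observed after attrition 240 × 0.5 = 120.
- Stage mix 35/40/25% (precontemplation/contemplation/preparation).
- Verified abstinence 4/9/20% by stage: 0.35×0.04 + 0.40×0.09 + 0.25×0.20 = 0.014 + 0.036 + 0.050 = 0.10, matching the protocol's overall rate.
- Reported abstinence 8/19/38%: 0.028 + 0.076 + 0.095 = 0.199, about 20%.
- Comments negative binomial with shape 0.5; mean by stage varied as in the table.
- Comments and abstinence independent within stage.

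**How the link arises.** Take mean comments of 6/12/24. Verified quitters are distributed over the stages as 0.014/0.10 = 14%, 0.036/0.10 = 36% and 0.050/0.10 = 50%. Non-quitters are distributed as 0.336/0.90 = 37.3%, 0.364/0.90 = 40.4% and 0.200/0.90 = 22.2%. Expected comments:
- quitters: 0.14×6 + 0.36×12 + 0.50×24 = 17.2
- non-quitters: 0.373×6 + 0.404×12 + 0.222×24 = 12.4

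The gap of nearly 5 comments comes from the stage mix alone.

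**Tests compared.** (a) The plain Mann-Whitney test. (b) A van Elteren test. In each stage s, with N_s participants of whom n_1s quit, let R_s be the rank sum of the quitters. The statistic is Σ w_s [R_s − n_1s(N_s+1)/2] with w_s = 1/(N_s+1), divided by its standard error. Each setting used 2,500 simulated trials at two-sided 5%.

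| Mean comments by stage | Preparation ÷ precontemplation | N | Verified: plain | Verified: stratified | Reported: plain | Reported: stratified |
|---|---|---|---|---|---|---|
| 12/12/12 | 1 | 120 | 5.3% | 4.9% | 4.6% | 5.0% |
| 12/12/12 | 1 | 240 | 4.6% | 4.4% | 4.8% | 5.1% |
| 10/12/15 | 1.5 | 120 | 5.6% | 4.3% | 6.4% | 4.7% |
| 10/12/15 | 1.5 | 240 | 6.1% | 5.0% | 6.6% | 5.0% |
| 8/12/18 | 2.25 | 120 | 6.9% | 5.0% | 9.4% | 5.2% |
| 8/12/18 | 2.25 | 240 | 9.2% | 4.8% | 11.8% | 5.2% |
| 6/12/24 | 4 | 120 | 9.0% | 3.6% | 13.9% | 4.6% |
| 6/12/24 | 4 | 240 | 14.6% | 4.1% | 23.4% | 4.6% |

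If stage is unrelated to quitting (10% in every stage; comments 6/12/24; N = 240), the plain test rejects in 5.4%. Both links are therefore needed.

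A second set of simulations at 10% overall abstinence, over comment gradients of 2- to 4-fold, gave 8-17% for the plain test, 6-7% with a weak gradient, about 5% with none, and about 4-6% for the stratified test. Taking both sets together, the plain test for verified abstinence rejects in about 7-10% at 120 and 9-17% at 240. The excess grows with sample size, as expected of a bias.

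**The case against.** **The stage-to-commenting link is not documented.** A reader might infer that stage drives commenting. The protocol does not say so. Every group receives 90 days of posts designed to elicit a response, and every group has weekly live sessions. The Background finding concerns survey respondents' interest, not comments by enrolled members. The CBT sessions run as Facebook events, and whether comments there count towards engagement is not stated. This objection stands: the claim must be that stage may influence commenting. The concern survives in that form, because the plan gives no protection if it does.

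**Incentive condition.** A reader might also infer that paying for comments confounds the comparison. It does not. Incentive conditions are randomised to groups already formed by stage. Unless the incentive affects quitting by some route other than commenting, and the document describes none, leaving it out creates no false link.

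**Size and stakes.** All comment gradients and stage-specific rates are assumed, and at the protocol's attrition the inflation for verified abstinence is modest. The question is the third item of a secondary aim, and the analysis section already uses the softer word. All of this stands and limits the weight of the point. It does not remove the mismatch between the aim's wording and what the test can show.

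**Conclusion.** The point holds as a minor one. The aim is worded as an effect, the exposure is self-selected, and the single planned test leaves out a recorded factor that the protocol itself calls related to outcomes. An association could therefore appear with no effect of engagement.

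How far this matters depends on how strongly comment counts differ by stage, which the documents do not show. The range runs from no inflation, through a negligible amount with a weak gradient, to roughly two or three times the nominal 5% for verified abstinence when preparation members comment several times as often and all 240 are observed. For reported abstinence, which is higher, the same gradients inflate the rate further.

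A reader might go further and conclude that the trial's main result is compromised. It is not: the comparison of TSP with control does not use comment counts.

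**What to change.** 1. Under Secondary analyses, replace the plain Mann-Whitney test of comments by 3-month abstinence with a rank test stratified by baseline stage of change (van Elteren), for both verified and reported abstinence.
2. In the Secondary Aim, reword the third item as the association of engagement with abstinence, in line with the analysis section. Stratification does not remove differences in motivation within a stage. Nor does it settle direction: comments accumulate over the same three months in which people quit, so early quitters may simply comment more.

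Cost: wording only, since stage is held for everyone. The downside is a small loss of information in strata with few or no quitters. With 120 participants and the assumed verified rates, expected quitters are 120×0.014 = 1.7 in precontemplation, 120×0.036 = 4.3 in contemplation and 120×0.050 = 6.0 in preparation, 12 in all. With so few events, stratifying on stage alone is about as much as the data will bear.

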## Discussion

To our knowledge, this is the first clinical trial of a smoking cessation intervention for young adults delivered entirely through Facebook. Intervention through social media is innovative and a particularly good option to reach young adult smokers, given widespread use and integration into the lives of users [19]. Yet intervention using this medium can be complicated with respect to recruitment and study design. For example, formative work with the study population indicated that a substantial minority of young adults, particularly those motivated to quit smoking, would be interested in a smoking cessation intervention delivered through Facebook [35]. Yet, a sample of 79 participants recruited for a feasibility trial was primarily white and male, limiting generalizability of the intervention results [36]. In the present trial, efforts are being made through targeted Facebook advertising to recruit a more diverse participant pool.

In this trial, we chose to compare TSP to a control condition in which participants were referred to the Smokefree.gov website. This remains a state-of-the-art digital treatment-as-usual, given scientific basis of its content, and free online access through multiple digital media. Given the overlap in medium and intervention content, significant results will provide strong evidence for the efficacy of TSP. While the content of TSP is similarly based on the Clinical Practice Guidelines, there are differences in the design and specific material presented, and the all-Facebook delivery is unique to TSP.

A key concern in using Facebook for intervention is participants’ privacy. Social media, by nature, is a public forum for interaction, and there is potential for unintended sharing of information. All TSP intervention components are administered entirely through private groups that are not visible beyond the participants in the groups. Participants are given detailed information about the intervention in the consent process, including notice that all groups are private. However, as in any interaction of social media, data belong to Facebook and their use is dictated by privacy agreements made between each user and Facebook itself, not a research investigator. Participants are made aware during the consent process that their TSP interactions are not completely private and that any concerns should be taken up with the investigators and Facebook itself. All assessments of smoking and other substance use in this study are administered outside of social media (i.e., Qualtrics website housed on a secure UCSF server). The Principal Investigator (first author) has obtained a Federal Certificate of Confidentiality from the NIH to protect all data from subpoena. Investigators have gone to great efforts to ensure that the exchange of information is this trial is used to make positive life changes with the support of an intimate network, and that limitations to privacy and confidentiality are clear to participants.

This trial will help to determine whether and how social media can be harnessed for long-term, biochemically verified smoking cessation in young adults.
